## Abstract

**Background:**

Persistent post-concussion symptoms (PCS) are associated with prolonged disability, reduced health-related quality of life and reduced workability. At present, no strong evidence for treatments for people with persistent PCS exists. Our research group developed a novel intervention, “Get going After concussIoN (GAIN)”, that incorporates multiple evidence-based strategies including prescribed exercise, cognitive behavioural therapy, and gradual return to activity advice. In a previous randomised trial, GAIN provided in a hospital setting was effective in reducing symptoms in 15–30-year-olds with PCS 2–6 months post-injury. In the current study, we describe the protocol for a trial designed to test the effectiveness of GAIN in a larger municipality setting. Additionally, we test the intervention within a broader age group and evaluate a broader range of outcomes. The primary hypothesis is that participants allocated to enhanced usual care plus GAIN report a higher reduction in PCS 3 months post-intervention compared to participants allocated to enhanced usual care only.

**Methods:**

The study is a stepped-wedge cluster-randomised trial with five clusters. The 8-week interdisciplinary GAIN program will be rolled out to clusters in 3-month intervals. Power calculation yield at least 180 participants to be enrolled. Primary outcome is mean change in PCS measured by the Rivermead Post-Concussion Symptoms Questionnaire from enrolment to 3 months after end of treatment. Secondary outcomes include participation in and satisfaction with everyday activities, labour market attachment and other behavioural measures. Self-reported outcomes are measured at baseline, by end of treatment and at 3, 6, and 18 months after end of treatment. Registry-based outcomes are measured up to 36 months after concussion.

**Discussion:**

The trial will provide important information concerning the effectiveness of the GAIN intervention in a municipality setting. Furthermore, it will provide knowledge of possible barriers and facilitators that may be relevant for future implementation of GAIN in different settings.

**Trial registration:**

The current GAIN trial is registered in ClinicalTrials.gov (study identifier: NCT04798885) on 20 October 2020.

**Supplementary Information:**

The online version contains supplementary material available at 10.1186/s13063-022-06572-7.

## Administrative information

Note: the numbers in curly brackets in this protocol refer to SPIRIT checklist item numbers. The order of the items has been modified to group similar items (see http://www.equator-network.org/reporting-guidelines/spirit-2013-statement-defining-standard-protocol-items-for-clinical-trials/).

## Introduction

### Background and rationale {6a}

Concussion, the mildest form of traumatic brain injury, is an important public health concern [1]. According to prospective studies, people reporting severe post-concussion symptoms (PCS) are associated with prolonged disability, reduced health-related quality of life and reduced workability [2–4]. Persistent PCS are associated with a high societal burden due to persistent impact on labour market attachment, and increased use of health care services and social welfare benefits [5]. It is estimated that persistent PCS such as headache, dizziness and sleep disturbances, are present in almost half of the affected persons 1-year post-injury [6].

Psychological factors are likely involved in the development of persistent PCS. In particular, negative illness perceptions worsen prognosis following concussion [7–9]. Furthermore, negative illness perceptions are associated with maladaptive illness behaviours such as avoiding activities, excessive rest, or the so-called all-or-nothing behaviour, i.e. oscillations between periods with very high or very low physical and mental activities [7, 10, 11]. Negative illness perceptions and maladaptive illness behaviours may act as symptom-perpetuating factors and reinforce PCS.

At present, no strong evidence for treatments for persistent PCS exists. However, recent systematic reviews and guidelines point toward principles from graded exercise therapy (GET), cognitive behavioural therapy (CBT) and a an interdisciplinary approach [12–15] may reduce symptoms or change illness behaviour and perception. These findings are in accordance with international guidelines for chronic pain management which also recommend CBT and GET [16, 17]. In line with this, three recent methodologically rigorous clinical trials demonstrated that an interdisciplinary intervention based on these principles were effective in reducing persistent PCS [14, 15, 18].

The intervention Get going After concussIoN (GAIN), was developed by the research group of the present study. GAIN was developed through a comprehensive process in a collaboration between people having had a concussion, therapists, experienced clinicians, and researchers [19]. The first GAIN trial (hereafter referred to as GAIN 1.0) tested the effect of GAIN delivered in a specialised hospital setting, among adolescents and young adults (15–30 years). In a randomised design, people having had a concussion receiving Enhanced Usual Care (EUC) plus GAIN (EUC + GAIN) showed a significantly larger reduction in PCS 3 months post-intervention compared to participants receiving EUC only. Furthermore, GAIN was demonstrated to be safe, feasible and associated with high participant satisfaction [19].

In recent years there has been an increased awareness of societal and personal consequences of persistent PCS in Denmark as well as internationally. Health care professionals and social workers point to the gap in knowledge concerning the management of persistent PCS in the community setting, and they urgently advocate for evidence-based treatment [20]. Therefore, we find it relevant to test the effectiveness of GAIN in a second trial (hereafter referred to as GAIN 2.0) in a larger scale in 16 of the 19 municipalities in the Central Denmark Region, where the majority of people who experience persistent PCS are being cared for by physical therapist and occupational therapists, social workers and general practitioners (GPs). Additionally, the GAIN 2.0 study will test the intervention within a broader age group and evaluate whether GAIN promotes people’s return to work and participation in everyday activities. Evidence from this study could facilitate wider uptake of GAIN, and thereby reduce personal and economic consequences of concussion.

### Objectives {7}

The overall aim of GAIN 2.0 is to test the effectiveness of EUC + GAIN in a municipality setting. The effect is measured as changes in self-reported PCS, self-reported participation in and satisfaction with instrumental activities of daily living (IADL), and labour market attachment.

#### Primary hypothesis

Participants allocated to EUC + GAIN report a greater reduction in PCS 3 months post-intervention compared to participants allocated to EUC only.

#### Secondary hypotheses

Participants allocated to EUC + GAIN report a greater increase in participation in IADL 3 months post-intervention compared to participants allocated to EUC only measured by the Utrecht Scale for Evaluation of Rehabilitation-Participation (USER-P) [21] as sum scores on the following dimensions: more time spend on, less limitations experienced in, and more satisfaction with participation in IADL.Participants allocated to EUC + GAIN have stronger labour market attachment 12 and 36 months post-concussion compared to participants allocated to EUC measured by sick leave, employment rate, and job stability.

### Trial design {8}

GAIN 2.0 is embedded in a regional, population-based cohort study—hereafter referred to as “the epidemiologic study”. GAIN 2.0 is a stepped-wedge cluster-randomised trial rolled out to clusters in 3-month intervals (Fig. 1). The trial consists of an 8-week interdisciplinary intervention programme (EUC + GAIN) against EUC only.

**Fig. 1 Fig1:**
[figure not shown]
The stepped wedge cluster randomised design. The stepped-wedge cluster randomised design with five clusters and six periods of each 3 months length. The white boxes illustrate the control condition (Enhanced Usual Care (EUC)) and the grey boxes intervention condition (EUC + Get Going After concussIoN (GAIN)). Recruitment, clinical assessment, and EUC take place 3 months period before each period illustrated in the figure. From power calculation, each box is estimated to involve a mean of 6 participants

## Methods: Participants, interventions and outcomes

### Study setting {9}

GAIN 2.0 is carried out in Central Denmark Region (population 1.3 million) as a collaboration between Hammel Neurorehabilitation Centre and University Research Clinic (HNC) and 16 of the regions’ 19 municipalities which are organised in five health clusters. GAIN is delivered at one or two specific locations in each of the five clusters.

GAIN 2.0 is embedded in an epidemiologic cohort study which includes people diagnosed with concussion at an emergency ward in Central Denmark Region and referred to the project by GP’s. The cohort is followed by means of questionnaires and health registers. People with PCS ≥ 20 on the Rivermead Post-Concussion Symptoms Questionnaire (RPQ) are recruited for the present study from May 2021 to November 2022.

### Eligibility criteria {10}

At enrolment, a clinical assessment of all participants is performed by medical doctors at the HNC. The clinical assessment consists of a neurological examination and a short, standardised medical history interview. Non-eligible participants are recommended to contact their GP for further advice if needed.

Participants are recruited based on the following inclusion criteria: (1) concussion caused by a head trauma according to the diagnostic criteria recommended by the Danish Consensus Report on Commotio Cerebri [22]. The criteria are based on recommendations by the WHO Task Force [2], but with the amendment, that there must have been a direct contact between the head and an object; (2) age 18 to 60 years at the time of the trauma; (3) a score of ≥ 20 on the RPQ within 1 week before enrolment in the study; (4) able to understand, speak and read Danish; (5) living in Central Denmark Region; and (6) identified from registers of the emergency departments or referred by GPs to GAIN 2.0 within 2–4 months after a concussion.

Exclusion criteria are (1) objective neurological findings and/or acute trauma CT scan indicating neurological disease or brain damage linked to the concussion, if performed; (2) previous concussion within the last 2 years with ongoing PCS at the time of the present concussion; (3) severe misuse of alcohol, prescription drugs and/or illegal drugs; (4) severe psychiatric co-morbidity (e.g. bipolar disorder, autism, psychotic disorder (life time) or severe neurological disease (e.g. multiple sclerosis) that impedes participation in the programme; and (5) inability to start the intervention within the maximum time for eligibility (4 months) plus the maximum possible waiting time from assessment to start of intervention (3 months), i.e. 7 months after concussion.

### Who will take informed consent? {26a}

Prior to the clinical assessment and inclusion in the GAIN 2.0 programme, written informed consent is obtained from each participant.

Informed consent is based on both the written information on the GAIN 2.0 project, which is emailed to potential participants prior to the clinical assessment and verbal information provided through a video or telephone consultation a week before the clinical assessment by a medical doctor. In case of no prior video or telephone consultation, the verbal information is provided by the medical doctor just before the clinical assessment. The medical doctors are not engaged in performing neither EUC nor GAIN intervention.

### Additional consent provisions for collection and use of participant data and biological specimens {26b}

The study does not involve biological specimens.

## Interventions

### Explanation for the choice of comparators {6b}

There is no strong evidence for any single intervention for people with persistent PCS. Supported by weak evidence [23], written or oral early information, reassurance and advice is a standard of care [24]. We consider it most ethically defensible to provide this standard of care (EUC) to all participants and compare the GAIN intervention to EUC only [15].

### Intervention description {11a}

#### *EUC* + *GAIN*

Participants allocated to EUC + GAIN will receive the GAIN intervention in the municipality. GAIN is an 8-week, interdisciplinary intervention programme that aims to achieve changes in negative illness perceptions and maladaptive behaviours. The intervention includes psychoeducation based on principles from CBT, GET and gradual return to daily activities e.g. coping strategies, behavioural reactions to symptoms in everyday living, individual goal-setting, and physical exercise facilitating the increase of frequency, intensity and time [19]. Furthermore, a toolbox regarding advise on specific shoulder and neck exercises, sleep behaviour, ergonomics and relaxation training is provided if relevant in individual cases. In short, the programme is structured as (1) three structured group sessions of 2 h duration in the first, second and eighth week, led by a neuropsychologist, an occupational- and a physiotherapist which aims to give participants a general knowledge. Relatives are invited to the first and the second session. (2) Up to five semi-structured and tailored individual sessions of 30 min duration with an allocated therapist (either an occupational- or a physiotherapist) dispersed over the weeks between the second and last group session. Furthermore, the neuropsychologist provides weekly supervision to therapists throughout the intervention period to ensure quality and fidelity. Each individual session is performed either in person or video by choice of the participant, and homework is required between each session. The number of individual sessions is flexible (a maximum of five), and adjusted according to the participant’s needs and goals. If neither a physical meeting nor video consultation was possible the individual session was arranged by telephone. The intervention is described in a manual which is available for the therapist involved in the intervention and will be released after the trial at the webpage of HNC.

### Criteria for discontinuing or modifying allocated interventions {11b}

Participants are informed that they are free to withdraw their consent and reject further participation in GAIN 2.0 at any time. Previous results from the GAIN 1.0 trial showed no adverse effects of the GAIN intervention and therefore we do not expect any adverse effects of the intervention in GAIN 2.0 either. Short symptom deterioration may be expected because of exposure to e.g. GET and the intervention will be adjusted according to follow individual tolerance.

### Strategies to improve adherence to interventions {11c}

To support adherence, GAIN incorporates personal goal-setting. Overall long-term goals are defined at the intervention start and short-term goals are then performed every week to be followed up in the next individual session.

### Relevant concomitant care permitted or prohibited during the trial {11d}

All five health clusters begin with a 3 months control period where each municipality offers usual services for people with persistent PCS. After 3 months, the first health cluster is randomly selected to initiate the GAIN intervention. The municipalities of the remaining clusters continue to offer their usual services including potential existing intervention programmes addressing persistent PCS, until their health cluster is assigned to initiate the GAIN intervention and then GAIN takes over as the municipality services that are provided. A cluster will be assigned to initiate GAIN every third month to allow the 8-week intervention to be performed within 3 months regardless of holidays. Correspondingly, participants are enrolled over periods of 3 months before intervention start. This design is necessary to get sufficient participants to start up group sessions of the GAIN programme. Consequently, participants may have a waiting period of up to 3 months after enrolment before beginning the GAIN intervention. During this period, therapists in the municipalities are allowed to provide a maximum of two sessions of usual services such as advice regarding return to work and IADL. To avoid contamination, therapists educated in GAIN will not perform usual services for participants in the waiting period. At the end of the trial period, the GAIN intervention is provided in all five clusters. During the 8-week GAIN intervention participants are recommended to (but not demanded to) pause any other treatment for persistent PCS.

### Provisions for post-trial care {30}

After the GAIN intervention, participants are free to continue or seek additional treatment for persistent PCS. Participants allocated to EUC are advised to seek further help from their GP if EUC is not sufficient.

### Outcomes {12}

Primary outcome is mean change in PCS level as measured by the RPQ from baseline to 3 months after end of treatment. RPQ is a 16-item, self-reported scale measuring the severity of PCS including physical (e.g. headaches or vomiting), cognitive (e.g. poor concentration or forgetfulness) and emotional (e.g. feeling frustrated or depressed) symptoms, within the past 24 h compared to before the injury on a five-point scale (ranging from 0 “not experienced at all” to 4 “a severe problem”, range: 0–64; furthermore, as previously recommended, scores of 1 counts as 0 which we also apply) [25].

Secondary outcomes include participation in IADL at 3 months after end of treatment, measured as the sum scores in each of the three dimensions (‘time spend on daily activities’, ‘experienced limitations’, and ‘satisfaction with participation’) on the USER-P [21]. USER-P is a disease-nonspecific questionnaire that measures IADL such as work, voluntary work, education, family duties and responsibilities, leisure activities, transportation, communication, and social activities. Additional secondary outcomes include labour market attachment assessed by using data from the DREAM register [26] (i.e. incidence of long-term sick leave defined as public assistance benefits related to illness in more than three consecutive weeks within 12 and 36 months of concussion), proportion of employed participants (defined as receiving no public assistance benefits except from state education fund grants at 12 and 36 months after concussion), and degree of job stability (based on whether labour market contributions have been paid in the 1-month period before 12 and 36 months after concussion). Measures of treatment targets (i.e., mechanistic outcomes) include the Brief Illness Perception Questionnaire (B-IPQ) [27] and the Behavioural Response to Illness Questionnaire (BRIQ) [28]. Additional secondary outcomes are listed in additional files (see, Additional file 1).

All self-reported outcomes are measured at baseline (within 1 week before clinical examination), at end of treatment and at 3, 6 and 18 months after end of treatment. Additionally, RPQ, BRIQ and B-IPQ are measured four times during intervention in the EUC + GAIN group. Furthermore, DREAM register data will be extracted up to 36 months after concussion.

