## Statistical methods

### Statistical methods for primary and secondary outcomes {20a}

Analyses are handled on an intention-to-treat basis. The primary outcome, RPQ, is analysed by using linear mixed-effects models with fixed effect of intervention arm and time (baseline, end of treatment, and 3 months after end of treatment) in interaction and random effects of clusters and subjects within clusters. Similarly, to evaluate clinical significance, we calculate the relative risk in each intervention arm of having an RPQ total score ≥ 20 at 3 months after end of treatment as well as the number needed to treat for prevention of one additional subject with RPQ total score ≥ 20. The secondary outcomes are analysed using linear mixed models similar to those described for the primary outcome using the secondary outcomes as dependent variables instead of RPQ. DREAM data will be analysed with time-to-event analysis and logistic regression.

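### The long-term sick-leave measure counts from the concussion, so spells that occurred before enrolment count as outcomes that neither arm can change

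*Protocol article*

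**What the plan says.** One secondary hypothesis concerns work: the intervention group is expected to "have stronger labour market attachment 12 and 36 months post-concussion compared to participants allocated to EUC measured by sick leave, employment rate, and job stability". Outcomes {12} then defines three register measures:

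- **Long-term sick leave:** the incidence of "public assistance benefits related to illness in more than three consecutive weeks within 12 and 36 months of concussion".
- **Employment:** status at 12 and at 36 months after concussion.
- **Job stability:** whether labour market contributions were paid in the month before each of those two dates.

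The first accumulates over a window that opens at the injury. The other two are read at, or just before, a fixed date.

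Eligibility criteria {10} require that participants be "identified from registers of the emergency departments or referred by GPs to GAIN 2.0 within 2–4 months after a concussion". Under Relevant concomitant care {11d}, "participants may have a waiting period of up to 3 months after enrolment before beginning the GAIN intervention".

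For the analysis, Statistical methods {20a} says "DREAM data will be analysed with time-to-event analysis and logistic regression" and, earlier, that analyses follow intention-to-treat. It states no time origin, risk set or rule for earlier spells. The adjusted models under Methods for additional analyses {20b} contain age, sex, previous mental health issues and recruitment route, but not sick leave before enrolment.

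**The concern.** A treatment comparison should count events that can still occur differently in the two arms. Here the window opens at the concussion, about 2 to 4 months before a participant can be enrolled. The event needs only a little over three weeks of illness-related benefit, which fits inside even the shortest interval. Such a participant enters the trial with the outcome already met, at 12 and at 36 months alike.

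Early spells are plausible in this population. Entry requires a Rivermead score of 20 or more at enrolment, and the Background {6a} itself links severe or persistent symptoms to reduced workability and greater use of welfare benefits.

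At stake is the first-named measure of the labour-market hypothesis. A real benefit could be reported as close to none. With only five clusters, all starting in EUC and crossing over in calendar order, a difference in earlier sick leave between control and intervention participants could also enter the estimate.

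**Working it through.** The plan gives no event rate, effect size or power for sick leave, so there is no figure of its own to reproduce.

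**Step 1. Share of the window before enrolment.** Inputs: entry at 2 to 4 months (Eligibility criteria {10}) and windows of 12 and 36 months (Outcomes {12}).

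- 12-month window: 2/12 = 17% and 4/12 = 33%.
- 36-month window: 2/36 = 6% and 4/36 = 11%.

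These are shares of time, not of events. An early spell fixes the participant as an event in both windows.

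**Step 2. Effect on the comparison.** Let q be the proportion with a qualifying spell before enrolment, equal in both arms. Among the rest, let p be the later risk under EUC and RR the true risk ratio. Counted from concussion:

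- Risk under EUC = q + (1 − q) × p
- Risk under EUC + GAIN = q + (1 − q) × p × RR
- Risk difference = (1 − q) × p × (1 − RR)

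The risk difference is therefore multiplied by (1 − q) whatever p and RR are. The observed risk ratio moves toward 1 because q is added to both numerator and denominator.

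**Step 3. Illustration.** All three inputs are assumptions: p = 0.30, RR = 0.60 (so 0.18 under GAIN), and q from 0 to 0.6. Power is for two proportions with 90 per arm, two-sided 5%, ignoring clustering and unequal allocation.

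| q | EUC | EUC + GAIN | Risk difference | Risk ratio | Approx. power |
|---|---|---|---|---|---|
| 0 | 30.0% | 18.0% | 12.0 points | 0.60 | 47% |
| 0.2 | 44.0% | 34.4% | 9.6 points | 0.78 | 26% |
| 0.4 | 58.0% | 50.8% | 7.2 points | 0.88 | 16% |
| 0.6 | 72.0% | 67.2% | 4.8 points | 0.93 | 10% |

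**Step 4. What an incident-spell analysis would recover.** Restricting to people without an earlier spell restores the risk ratio of 0.60 but leaves 90 × (1 − q) per arm: 72, 54 and 36. Approximate power is then 39%, 31% and 22% for q = 0.2, 0.4 and 0.6, against 26%, 16% and 10% when counting from concussion. The gain is real, but the 47% in the first row is not recoverable by exclusion.

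**Step 5. Unequal early spells.** Suppose GAIN has no effect on later risk (30% in both arms) and q is 0.40 under EUC. With q = 0.35 under EUC + GAIN, the risks are 58.0% and 0.35 + 0.65 × 0.30 = 54.5%, an apparent benefit of 3.5 points. With q = 0.45 they are 58.0% and 0.45 + 0.55 × 0.30 = 61.5%, an apparent harm of 3.5 points. The direction depends only on where the early spells fall.

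**The case against.** **The whole hypothesis looks affected, but it is not.** A reader might infer that the labour-market effect as such is diluted. Employment and job stability are measured at or just before 12 and 36 months and do not accumulate earlier events.

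**The wait for GAIN looks like part of the defect, but it is not.** GAIN may begin as late as the "maximum possible waiting time from assessment to start of intervention (3 months), i.e. 7 months after concussion". One could compute 7/12 = 58% and say that over half of the 12-month window precedes treatment. The documents do not support counting the wait. The analysis is by intention-to-treat, the cluster schedule was generated before trial start (Sequence generation {16a}), and each participant's group is registered within two weeks of the clinical assessment (Implementation {16c}). Time after that belongs to the assigned arm. Only the period before enrolment is at issue.

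**The time origin of the survival analysis is not stated.** This stands. {20a} names methods only, and risk-set details may properly sit in an analysis plan that is not shown. The term incidence could also be read as new cases among people at risk. It follows that no claim about a hazard ratio can be made from this text. But the outcome definition does state its window, counted from the concussion, and an analysis plan that follows it inherits the problem. A logistic regression on that definition has it without any further assumption.

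**The size is assumed, and the bias may be conservative.** Both are correct. The documents give no sick-leave rates, and with equal early spells the result is attenuation. The 12-point and 4.8-point differences also refer to different groups, the event-free and everyone; the number of spells prevented is the same. What is lost is precision and a risk ratio that describes the treatment. Unequal early spells are ordinary baseline imbalance, for which the documents give no evidence either way, but the listed covariates would not correct it.

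**Conclusion.** The point holds for the long-term sick-leave measure, one of three under the labour-market hypothesis. It rests on a definition the protocol states, not on missing detail: about 17–33% of the 12-month window and 6–11% of the 36-month window precede enrolment, and spells in that time are events neither arm can alter.

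With early spells equally common in both arms, the risk difference shrinks by exactly the share of participants already counted and the risk ratio moves toward 1. With unequal early spells the bias can go either way. The risk ratios of 0.78, 0.88 and 0.93 rest wholly on assumed values and show how the estimate would behave, not what this trial will find. The primary outcome is untouched. The change should be made, but it is not critical to the trial's main conclusion.

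**What to change.** For the sick-leave measure, in both arms:

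1. Start the clock at the clinical-assessment (enrolment) date. It exists in both arms and precedes the notice of allocation. Keep 12 and 36 months after concussion as the end of the window if wished.
2. Count only spells that begin after that date or, so that people already on benefit are kept, analyse weeks on benefit after enrolment.
3. Adjust for sick-leave weeks between concussion and enrolment.
4. State that events during the waiting period stay with the assigned arm under intention-to-treat.

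Do not start the clock at the first GAIN session. That date exists in one arm only and would create immortal time there.

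The cost is a change of wording in the outcome definition and analysis. The present definition already needs DREAM data from the concussion onward, so no new data are required. There are two small downsides: an incident-spell analysis has fewer people at risk, and the measure is no longer directly comparable with incidence counted from concussion in the wider cohort. The latter could still be reported descriptively.
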